#### Parenting self-regulation scale (PSRS)

The 12-item Parenting Self-regulation Scale (PSRS) [48] will be used to assess parents’ self-regulatory capacity in their parenting role. The PSRS has a single factor structure and demonstrated excellent internal consistency (α = 0.92). Each item will be rated on a Likert scale from 1 (strongly disagree) to 7 (strongly agree). A total score is calculated by summing all items. Higher scores reflect higher parenting self-regulation.

#### Child Adjustment and parent efficacy scale (CAPES)

Children’s social, emotional, and behavioral difficulties, as well as their parents’ confidence in managing the parenting challenges will be assessed by an extended version of the Child Adjustment and Parent Efficacy Scale (CAPES) [49]. The original CAPES has 27 items to measure the intensity of child emotional and behavioral problems, with a 3-item emotional maladjustment and a 24-item problem behavior subscale. The internal consistency for the total intensity subscale and the subscales ranges from adequate to excellent (α = 0.90, 0.90, and 0.74 respectively). Item ratings are indicated on a 4-point Likert scale of 0 (not true of my child at all) to 3 (true of my child very much). Nineteen items describe negative behavior, and eight reverse-coded items describe positive behavior. Parents are also asked to rate their confidence in managing each of the negative behaviors using a scale of 1 (certain I can’t do it) to 10 (certain I can do it). The sum of the 19 confidence ratings generates the Efficacy scale of the CAPES, which has excellence internal consistency (α = 0.95). In the present study, five items have been added to capture children’s social difficulties with peers, through three negatively worded items (e.g., “*my child has no one to play with*”) and two positively stated items (e.g., “my child has close friendships at school”). Parents are required to provide confidence ratings for each of the negative statements.

#### Partner in Education Survey (PIES)

The Partner in Education Survey (PIES) [50] is a parent-report measure the Home-School Partnership for parents of children ages 5 to 12 years attending primary school. This 18-item measure can be completed by a cross-section of parents from differing backgrounds and education levels and, as such, the comprehension level and readability were considered. The PIES has a Flesch-Kincaid Grade Level of 7.2. This readability statistic means that the survey is able to be understood by someone who has obtained at least grade seven schooling or seven years equivalent education. The PIES contains five sub-scales: Parent-Teacher-Communication, Parent-School Communication, Home Involvement, Parental-School Contribution and Working with the Community with three additional items being retained due to their clinical significance (*I value learning and try to communicate this value to my child*, *I feel comfortable talk* and *My child’s teacher and I have mutual respect for one another*). Parents respond to each item on a 10-point Likert-type response scale ranging from 1 *never/not at all* to 10 *always/very much*. An overall score is calculated by summing the total of all responses with higher scores representing more positive parental perceptions of the Home-School Partnership. The internal consistency of the total scale is excellent (α = 0.92).

#### Parenting an anxious child questionnaire (PACQ)

Parenting an Anxious Child Questionnaire (PACQ) [51] is used to assess parental responses and confidence in managing children’s anxiety. PACQ has 12 items, where 11 items assess parents’ frequency of using each specific parenting strategy and the 12th item assesses parents’ overall confidence in managing children anxiety. Items are rated on a five-point Likert-scale ranging from 0 (Never) to 4 (Always). The sum of item ratings (with three reverse-coded items) is used to calculate the total score.

#### Brief Spence Children’s anxiety scale (BSCAS)

Child anxiety symptoms will be measured with the parent-report version of the Brief Spence Children’s Anxiety Scale (BSCAS) [52], which is an abbreviated version of the Spence Children’s Anxiety Scale – Parent version [53]. The BSCAS is an 8-item, single factor measure with adequate to good internal consistency (α = 0.73-0.82 in different samples). Parents rate their responses on a four-point Likert scale, ranging from 0 (Never) to 3 (Always). A measure score is calculated by summing all the items; higher scores indicate higher levels of child anxiety.

#### Preschool feelings Checklist (PFC)

The Preschool Feelings Checklist (PFC) [54] is a 16-item checklist of children depression symptoms. The PFC contains 16 statements about child mood and depression where parents answer yes/no for each statement. The PFC has acceptable internal consistency (α = 0.76). The sum of scores is used to calculate the PFC score with higher scores suggesting higher levels of paediatric depression.

#### Parent satisfaction survey (PSS)

The Parent Satisfaction Survey (PSS) [55] evaluates parents’ perceptions of the overall quality of the Triple P seminar series. The PSS consists of 10 items capturing different aspects of the seminars. Parents rate their response on a 7-point Likert-scale ranging from 1 (*poor/no, definitely not*) to 7 (*excellent/yes, definitely*). Parents are also asked to provide general comments about the seminar series.

#### Analytic plan

Only non-identifiable data will be included in analysis. The patterns of the data missingness will be tested and appropriately addressed prior to the analysis of outcome variables. If the missingness is deemed to be Missing Completely at Random or Missing at Random, Full-information Maximum Likelihood (FIML) estimation or expectation maximisation algorism (EM) will be used to impute the missing data [56]. Following an intention-to-treat protocol, a Piecewise Latent Growth Curve Model (Piecewise LGCM) will be tested for each outcome variable, which allows the estimation of the rate of change between the pre-intervention assessment and the post-intervention assessment and the rate of change between the post-intervention assessment and the follow-up assessment. If the school level variance is substantial due to the nested nature of sample, a multi-level Piecewise LGCM will be used. School and individual level control variables might be included in the model (see Fig. 2 for the proposed model). To examine the differences between conditions, appropriate analytic options for the present study design will include but not limit to multigroup ML-Piecewise LGCM and visual analysis using Brinley Plots [57].

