### Outcomes

A comprehensive set of measures will be administered to track changes in child and family related outcomes over time. Parent-report survey data will be collected online, through the Qualtrics survey platform at baseline (T1), post-intervention (T2; 6 weeks after T1), and follow-up (T3; 12 weeks after T1). At each assessment point, the online survey will take about 15 to 20 min to complete. A prize draw for gift vouchers was introduced to increase the survey response rate at T2 and T3. Participants will not be informed about the introduction of the prize draw prior to the due date of the survey. Data will be stored in Australia on secure university servers. Table 2 displays detailed information about when each measure will be administered. Below is a list of descriptions for each individual measure.

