## Discussion

The findings from this study will extend our current knowledge of the effects of evidence-based parenting support delivered through brief, universally offered, low intensity parenting seminars and delivered in school settings. The approach adopted is consistent with the multi-level conceptual model of evidence-based parenting support for educational settings as outlined by Sanders, Healy [58]. The model highlights the unique value of the school setting to help normalize and destigmatize parenting programs and thereby increase parental engagement and widen the reach of parenting programs.

The intervention being tested builds on previous studies showing that a brief three session Triple P seminar series on positive parenting can be effective in changing parenting practices and in improving children’s behavior and adjustment [16, 19, 23]. It extends earlier work by concurrently addressing in the same program, parents’ concerns about their children’s behavior problems, anxiety and peer relationships, particularly school bullying. As the seminar series is a low intensity, brief intervention (Level 2 in the multilevel Triple P system) it is expected that a minority of children and parents with more complex problems may require additional support.

The sample size we intend to recruit will be large enough to examine important moderators of intervention outcomes for both child and parent outcomes including parental completion rates. These moderators include the type of school (state, Catholic, or independent school), the relative social disadvantage of schools, child and parent age and gender, family characteristics (e.g. single parent household), ethnicity, the baseline severity of child social, emotional and behavioral problems, parenting practices and level of program participation such as the number of seminars parents attended. These analyses will help identify the profiles of children and parents who might require early additional support to complete the series and lead to a more nuanced understanding of the reasons for non-completion. As each of the individual seminars are presented as a package and introduced as being relevant to every child, it is likely that some parents would be particularly interested in certain topic and less interested in others. Parents and teachers’ evaluations of the seminars themselves will provide additional end user/consumer feedback to enable the program to adapt and evolve [59, 60].

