The interpretation of findings from this study will need to take into account the study’s relative strengths and limitations. Relative strengths include recruiting a large number of schools and parents and the socioeconomic diversity of the schools involved that included state public schools, Catholic Schools and independent schools. The outcome assessments will include reliable, validated and change sensitive assessment tools. The experimental design will enable the program to be sequentially introduced, across the school year, using an incomplete stepped wedge cluster randomised trial design. This variant of the stepped wedge design is particularly useful in evaluating programs in schools. This design involves a systematic replication of intervention effects, with schools servicing as their own controls, rather than relying on randomisation of schools to different conditions e.g., where the intervention is withheld altogether, not available, or only after long delays as in care as usual and waitlist control designs. Traditional RCT’s can be very difficult to implement in regular school settings with differential attrition between intervention and control schools being a particular concern. Another unique feature of the approach will be the inclusion of an intervention component, via a teacher webinar, that will provide guidance to teachers on how to support parents participating in the parenting seminar series. It is widely recognised that improved home-school communication can greatly benefits children’s experience of school, their learning and social and emotional wellbeing, all of which had been adversely affected by COVID-19 [4].

The relative weaknesses of the study include reliance on parents (likely to be disproportionately mothers) as the primary informant for gauging intervention effects. Although parents are the primary target of the intervention and, as such, are crucially important informants about their experience, it is not possible to independently verify parent reported change in their children’s behavior, anxiety or peer relationships. It would have been valuable to plan collection of independent teacher observation data on the child outcomes; however, this is precluded as based on the ethical reasons, teachers were not able to be informed which parents at their school had actually attended the online seminars which were generally scheduled out of school hours.

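### A test of missingness cannot establish MAR, and the missing-data step leaves out seminar attendance; the intention-to-treat change would be overstated if non-attenders answer less and change less

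*Protocol article*

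**What the plan says.** The Analytic plan opens its handling of missing data with a test: "The patterns of the data missingness will be tested and appropriately addressed prior to the analysis of outcome variables". The method depends on the result: "If the missingness is deemed to be Missing Completely at Random or Missing at Random, Full-information Maximum Likelihood (FIML) estimation" or EM is applied. No method is named for data judged not to be MAR.

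The outcome analysis follows: "Following an intention-to-treat protocol, a Piecewise Latent Growth Curve Model (Piecewise LGCM) will be tested for each outcome variable". It estimates one rate of change from T1 to T2 and another from T2 to T3. Covariates are left open: "School and individual level control variables might be included in the model". None is named in the text.

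Attendance appears in the Discussion, in the list of moderators to be examined: "level of program participation such as the number of seminars parents attended". The same paragraph expects that not every parent will finish the series, and hopes the moderator analyses will "lead to a more nuanced understanding of the reasons for non-completion". The Outcomes section shows that survey non-response is also a concern: "A prize draw for gift vouchers was introduced to increase the survey response rate at T2 and T3". No rate is given for attendance or for response, and no link between them is stated.

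**The concern.** There are two linked problems.

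First, the decision rule cannot do what it says. Whether data are MAR or MNAR depends on values that were not observed. A test on observed data can show that missingness is related to something measured, which rejects MCAR. It cannot show that nothing unmeasured is at work. The rule treats an untestable assumption as a finding and is silent on the other outcome of its own condition.

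Second, the model described has little information about the parents most likely to matter. A parent who registers, attends no seminar and skips T2 and T3 is represented by a T1 score and by the change seen in parents who did answer. If those are mainly attenders, the silent non-attender is in effect given an attender's change.

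At stake is the meaning of the intention-to-treat label. For a universal, low-intensity offer, the change among all parents who registered is the quantity of interest, and it could drift toward the change among those who stayed. Comparing the two conditions would not remove this. In Table 1, both steps move from baseline to a post-intervention assessment between T1 and T2, so similar attrition in both would inflate both changes.

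**Working it through.** **Figure to reproduce.** The article gives none on this point, because it states no attendance or response rate. The power statement does not involve either.

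**Inputs, all assumed except where noted.** pA and pN are the shares of parents who attend and do not attend. rA and rN are their T2 response rates. dA and dN are their mean T1–T2 improvements in SD units. The value 0.30 is borrowed from the sample-size paragraph for scale only; the article does not say it applies to attenders alone.

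**Formulas.** With T1 complete, attendance unrelated to T1, and parents who miss T2 also missing T3, maximum likelihood under MAR without attendance gives non-responders the responders' change:

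- True intention-to-treat change = pA·dA + pN·dN
- Estimate without attendance = (pA·rA·dA + pN·rN·dN) / (pA·rA + pN·rN)
- Difference = (dA − dN) × (attenders' share among responders − pA)

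The last line shows that both conditions are needed. The bias is zero if attenders and non-attenders change alike (dA = dN) or respond alike (rA = rN).

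**Results.**

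| Attend | Response, attenders / non-attenders | Change, attenders / non-attenders | True | Estimate without attendance | Ratio |
|---|---|---|---|---|---|
| 60% | 70% / 70% | 0.30 / 0 | 0.180 | 0.126/0.70 = 0.180 | 1.00 |
| 70% | 80% / 50% | 0.30 / 0.10 | 0.240 | (0.168 + 0.015)/0.71 = 0.258 | 1.07 |
| 60% | 80% / 40% | 0.30 / 0 | 0.180 | 0.144/0.64 = 0.225 | 1.25 |
| 50% | 80% / 30% | 0.30 / 0 | 0.150 | 0.120/0.55 = 0.218 | 1.45 |

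Check of the third row by the difference formula: attenders are 0.48/0.64 = 75% of responders, so the difference is 0.30 × (0.75 − 0.60) = 0.045, and 0.180 + 0.045 = 0.225.

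**Simulation.** With 300,000 parents and a T1–T2 correlation of 0.6, the fourth row gave 0.219 and the second 0.260 (about 8% over). With 400,000 parents and a correlation of 0.7, the third row gave 0.225, and 0.224 when attendance also depended on T1.

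**Wider grid.** With attender response at 80%, non-attender response falling from 60% to 20%, and changes of 0.30 and 0, the ratio runs from 1.05 to 1.18 at 80% attending, 1.11 to 1.43 at 60%, and 1.18 to 1.82 at 40%.

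**With attendance as an auxiliary variable.** The third-row estimate returns to 0.180. This holds by construction, because missingness was generated from attendance alone. When response also rose by 10 percentage points per SD of improvement, the true change was 0.182, the estimate without attendance 0.306 and with it 0.269. Of the excess of 0.124, 0.087 (about 70%) remained.

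**The case against.** The strongest reply is that this is a condensed article. Auxiliary variables and sensitivity analyses belong in a full analysis plan, which is not shown, and neither is the content of Fig. 2. The text says patterns will be addressed appropriately and leaves covariates open, so nothing excludes attendance. This stands as far as the absence of detail goes. It does not rescue the decision rule, which the article prints and which cannot work as printed.

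Several stronger readings are tempting and are not supported:

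- **That the intention-to-treat change is biased.** The documents give no rates and no link between attendance and response. Parents register themselves and must be able to attend three sessions, and the prize draw rewards survey response, not attendance. Both could weaken such a link.
- **That the plan ignores attendance.** It uses attendance as a moderator; the gap is confined to the missing-data step.
- **That the remark that "teachers were not able to be informed which parents at their school had actually attended the online seminars" shows attendance is linked to the survey data.** It concerns disclosure to teachers. Only the moderator sentence implies that attendance will be available for analysis.
- **That the model uses only earlier scores.** FIML uses every observed wave, so a parent who misses T2 but answers T3 contributes T3. The two-wave working is exact only where T3 is missing as well, and it yields no figure for the T2–T3 change.
- **That adding attendance cures the problem.** It does so only if attendance accounts for the missingness.

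**Conclusion.** The point holds in a conditional form. What is certain is that a test on observed data cannot justify MAR, so the rule in the Analytic plan is badly fixed and should go. It is also clear that the text does not connect attendance with the missing-data handling.

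The bias itself is a risk and not a demonstrated fault. It needs non-attenders both to answer less often and to change less. Under the assumed rates it runs from nothing, when response is unrelated to attendance, through about 7–8% and 25%, to about 45% at 50% attending with 80% and 30% response. In absolute terms that is 0 to about 0.07 SD (0.218 − 0.150). More extreme assumptions give more. The figures concern the T1–T2 change only.

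The change is worth making before analysis because it is cheap, should use data the team already plans to analyse, and protects the meaning of the intention-to-treat result.

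**What to change.** 1. Delete the rule under which a missingness test selects the method. Missingness patterns can still be described.
2. State FIML, under an assumed MAR mechanism, as the primary method for all outcomes.
3. Include the number of seminars attended (0–3) and the baseline predictors of non-response as auxiliary variables, entered as saturated correlates. Attendance arises after baseline, so it should inform the missing scores and not enter the effect model as a covariate.
4. Add one pattern-mixture sensitivity analysis in which non-responding parents who attended no seminar or one seminar are set to no change from T1. This is needed because attendance alone does not remove MNAR bias.

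The cost is revised analysis wording and a few extra model runs, with no new data collection. The one downside is that the reported effect may be less favourable.

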### Participants and recruitment

The study will involve at least 300 Australian primary schools, from three Australian states, South Australia, Queensland, and Victoria. Following the receipt of relevant ethical clearance, school leaders will be notified about the Thriving Kids and Parents Schools Project through multiple channels (e.g., emails, principal, and parent associations). Priority will be given to government (state-funded) and Catholic schools and if funding permits, independent schools will subsequently be invited to participate. Initial school engagement will utilise an expression of interest (EOI) approach with interested schools being required to complete an EOI form. Following completion of an EOI, further project information will be provided and processes regarding participation negotiated.

Using promotional materials produced by the project team, participating schools will invite their parent body to register online to participate in the TKPSP seminar series. The promotional materials will be specifically targeting schools’ multiple communication channels with the aim of recruiting as many parents as possible. In order to appeal to a wide audience, parents’ eligibility will be determined using the following broad inclusion criteria: (1) presence in the family of at least one child of primary-school age; (2) interested in information about parenting and child development; (3) able to attend online seminars on three separate occasions. Parents will be required to register online and consent to participate will be collected during the registration process.

Utilising the method introduced by Hemming and colleagues [38, 39], assuming an effect size of 0.30 with a type one error rate of 0.001 and an intra-cluster correlation coefficient of 0.05, engaging 50 schools in each batch with an average of more than 10 parents per school will produce sufficient statistical power (> 0.90).

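### The plan permits EM imputation as an alternative to FIML, with nothing to carry imputation uncertainty into the standard errors; one EM-filled data set analysed as observed would make them too small

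*Protocol article*

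**What the plan says.** The Analytic plan section of the protocol article sets out three steps.

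1. Timing: "The patterns of the data missingness will be tested and appropriately addressed prior to the analysis of outcome variables".
2. Condition and method: "If the missingness is deemed to be Missing Completely at Random or Missing at Random", then "Full-information Maximum Likelihood (FIML) estimation or expectation maximisation algorism (EM) will be used to impute the missing data".
3. Analysis: under intention to treat, "a Piecewise Latent Growth Curve Model (Piecewise LGCM) will be tested for each outcome variable". The model becomes multilevel if school-level variance is substantial.

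The section gives no rule for choosing FIML or EM. It mentions no multiple imputation, bootstrap or other variance correction.

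The Outcomes section places the surveys "at baseline (T1), post-intervention (T2; 6 weeks after T1), and follow-up (T3; 12 weeks after T1"). It adds: "A prize draw for gift vouchers was introduced to increase the survey response rate at T2 and T3". Non-response is therefore a recognised concern, but the article gives no expected or observed response rate.

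**The concern.** The sentence treats FIML and EM as two ways of doing the same thing, and they need not be. FIML fits the growth model to the observed scores and fills in nothing; under missing at random its standard errors are valid. EM used for imputation replaces each missing score with a prediction. If the outcome model then reads that file as complete, predictions count as data. The point estimate of mean change can be sound while its standard error is too small, so tests reject too often even when the missing-at-random assumption is true. As one growth model is planned per outcome, the same fault could recur across outcomes.

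The condition attached to the method is a lesser, related problem. It makes the method depend on missingness being judged completely at random or at random after testing. Observed data can contradict missing completely at random, but they cannot separate missing at random from missing not at random. The stated test therefore cannot establish the stated condition.

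**Working it through.** **The plan's own figure.** The only computed figure is in Participants and recruitment, where power above 0.90 is claimed "assuming an effect size of 0.30 with a type one error rate of 0.001 and an intra-cluster correlation coefficient of 0.05". The claim counts 50 schools per batch and upwards of 10 parents from each. As a parallel-cluster approximation, three batches of 50 schools give 75 schools per arm. With 10 parents each, the design effect is 1 + 9 × 0.05 = 1.45 and the effective number per arm is 750/1.45 = 517. Two-sided power is 0.937, which agrees with the statement. The present point does not depend on this figure.

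**Inputs assumed, because the article gives none.** Share observed at T2: o. T1-T2 correlation: r = 0.6. Unit variance at each wave, T1 complete, no clustering, large samples.

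**Formulas.** Write T2 = r·T1 + residual, with residual variance 1 − r².

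- True variance of the estimated mean change: [(1 − r²)/o + (1 − r)²]/n. Only the observed share o informs the residual part.
- Variance reported after one conditional-mean EM fill: [o(1 − r²) + (1 − r)²]/n. Filled cases contribute no residual scatter but are counted in n.
- SE ratio: square root of reported over true. Actual size at nominal two-sided 0.05: 2[1 − Φ(1.96 × ratio)].

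With r = 0.6, 1 − r² = 0.64 and (1 − r)² = 0.16. The ratio is the same for the difference between two equal arms with equal missingness.

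| Missing at T2 | n × true variance | n × reported variance | SE ratio | Actual size at 0.05 |
|---|---|---|---|---|
| 5% | 0.64/0.95 + 0.16 = 0.834 | 0.608 + 0.16 = 0.768 | 0.96 | 0.06 |
| 10% | 0.64/0.90 + 0.16 = 0.871 | 0.576 + 0.16 = 0.736 | 0.92 | 0.07 |
| 20% | 0.64/0.80 + 0.16 = 0.960 | 0.512 + 0.16 = 0.672 | 0.84 | 0.10 |
| 30% | 0.64/0.70 + 0.16 = 1.074 | 0.448 + 0.16 = 0.608 | 0.75 | 0.14 |
| 40% | 0.64/0.60 + 0.16 = 1.227 | 0.384 + 0.16 = 0.544 | 0.67 | 0.19 |

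A simulation of 4,000 data sets of n = 1,500 at 40% missing gave a size of 0.195.

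**Independent check with arms, three waves and missing at random.** Two arms of 300 parents, no true effect, missingness depending on baseline, EM fitted within arm, wave correlation 0.5 or 0.7, 600 replicates, no clustering. The test was the arm difference in T1-to-T2 change at nominal two-sided 0.05.

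| Missing at T2 (about) | FIML: size | One EM conditional-mean fill: SE ratio; size | One EM fill with random residuals: SE ratio; size |
|---|---|---|---|
| 20% | 0.050–0.060 | 0.81–0.82; 0.10–0.11 | 0.83–0.84; 0.10 |
| 40% | 0.040–0.058 | 0.66–0.67; 0.19–0.21 | 0.73; 0.14–0.16 |
| 60% | 0.052–0.062 | 0.46–0.50; 0.34–0.38 | 0.59–0.63; 0.23–0.25 |

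FIML standard errors were 0.96 to 1.01 of the true sampling standard deviation. With 600 replicates, the Monte Carlo standard error of a size of 0.05 is √(0.05 × 0.95/600) = 0.009, so the FIML sizes are compatible with nominal. Adding random residuals to a single fill reduces the fault but does not remove it.

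**The case against.** The strongest reply is that the damaging procedure is inferred. The section does not say that EM fills each score once, or that the filled file is analysed as complete. The same verb covers FIML, which fills in nothing, so it may be loose wording for handling missing data. EM could then mean maximum likelihood estimation by the EM algorithm. With standard errors from the observed-data likelihood, that is sound. FIML is also named first and can fit the planned model directly. This stands in part: the point must be conditional. It does not remove the point, because the text places the handling before the outcome analysis and calls it imputation, so a single EM fill complies with the plan as written.

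Three stronger readings are tempting, and the article supports none of them.

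- A reader might infer that precision will be overstated for every outcome. That needs EM to be chosen, used as a single fill, and applied to appreciable missingness in each outcome. The prize draw shows a wish for more responses but gives no rate, and at 5% to 10% missing the effect is mild.
- A reader might carry the inflation over to a 0.001 test level. The article uses 0.001 only in the power calculation; the Analytic plan states no test level.
- A reader might count the absence of a sensitivity analysis for data missing not at random, or of a named list of covariates, as a defect. A journal article may leave such detail to the full protocol or SAP, which is not shown.

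Neither the formula nor the simulation includes school clustering, although the power calculation assumes an intra-cluster correlation of 0.05. The figures show the direction and rough scale of the error and are not estimates for this trial.

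**Conclusion.** The point holds conditionally. The Analytic plan permits EM imputation in place of FIML, gives no rule for choosing, and provides nothing that carries imputation uncertainty into the standard errors. Under a single fill analysed as observed, and with the assumptions above, the understatement of the standard error runs from about 4% at 5% missing to about 33% at 40% missing. The size of a nominal 0.05 test rises correspondingly from about 0.06 to 0.19. The true missing fraction is not in the article, so where this trial falls in that range is unknown. With FIML, or with EM used only for estimation alongside observed-data standard errors, this fault is absent and what remains is unclear wording. The change is still worth making because it closes off an invalid route at almost no cost.

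**What to change.** In the Analytic plan:

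1. Delete EM as an imputation option. State that the piecewise growth model, multilevel where applicable, is fitted by FIML to all available observed data, with no filled-in data set.
2. If imputation is needed for some purpose, specify multiple imputation that respects the school level, combined by Rubin's rules.
3. State missing at random as an assumption of the analysis. Missingness patterns can still be described, but should not be presented as establishing that assumption.

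The cost is a change of wording, since FIML is already the first-named method and suits the planned model. No change to design, data collection or sample size follows.
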